## Abstract

**Background:**

Cardiovascular disease is the leading cause of mortality in the United States. Maintaining healthy levels of physical activity is critical to cardiovascular health, but many older adults are inactive. There is a growing body of evidence linking low motivation and inactivity. Standard behavioral counseling techniques used within the primary care setting strive to increase motivation, but often do not emphasize the key component of self-control. The addition of electronic activity monitors (EAMs) to counseling protocols may provide more effective behavior change and increase overall motivation for exercise through interactive self-monitoring, feedback, and social support from other users.

**Objective:**

The objective of the study is to conduct a three month intervention trial that will test the feasibility of adding an EAM system to brief counseling within a primary care setting. Participants (n=40) will be randomized to receive evidence-based brief counseling plus either an EAM or a pedometer.

**Methods:**

Throughout the intervention, we will test its feasibility and acceptability, the change in primary outcomes (cardiovascular risk and physical activity), and the change in secondary outcomes (adherence, weight and body composition, health status, motivation, physical function, psychological feelings, and self-regulation). Upon completion of the intervention, we will also conduct focus groups with the participants and with primary care stakeholders.

**Results:**

The study started recruitment in October 2015 and is scheduled to be completed by October 2016.

**Conclusions:**

This project will lay the groundwork and establish the infrastructure for intervention refinement and ultimately translation within the primary care setting in order to prevent cardiovascular disease on a population level.

**Trial Registration:**

ClinicalTrails.gov NCT02554435; https://clinicaltrials.gov/ct2/show/NCT02554435 (Archived by WebCite at http://www.webcitation/6fUlW5tdT)

## Introduction

### Cardiovascular Disease and Physical Activity

In the United States, more than 85 million adults have at least one type of cardiovascular disease (CVD) [1]. It is the most deadly disease in the United States (accounting for 1 in 3 deaths) and the world [1,2]. By 2020, the American Heart Association (AHA) strives to reduce this number by 20% [3]. It is well established that lifestyle behaviors, such as physical activity (PA), are related to CVD [4-9]. Therefore, intervening on PA is an important step toward meeting this goal [10]. The Centers for Disease Control recommendation for primary and secondary prevention of CVD is 30 minutes of PA a day, 6-7 days per week [7]. However, analysis of the Behavioral Risk Factor Surveillance System reports the prevalence of older adults meeting this recommendation only reaches 39.3% [11]. Lack of motivation to exercise appears to be a barrier that impedes meeting the recommendation for many older adults [12].

A promising strategy for increasing motivation for exercise is promotion by primary care providers [13-16]. The United States Preventive Services Task Force (USPSTF) developed the 5 A’s counseling intervention to be used in the primary care setting [17]. The components of 5 A’s stand for assess, advise, agree, assist, and arrange. Five A’s is a comprehensive and validated counseling technique to elicit behavioral change during a typical medical visit [10,17]. This counseling is based on the Self-Determination Theory, which targets perceptions of autonomy, competence, and relatedness to increase autonomous motivation, that is, motivation that is volitional and internal rather than external [18,19].

Most primary care physicians use at least one 5 A’s measure with their patients [20]; however, comprehensive behavioral counseling or complete 5 A’s counseling is not routinely conducted [15,20]. Even if proper 5 A’s counseling was done routinely, providing knowledge and professional support alone is insufficient for changing behavior [21]. Emphasizing self-control through self-monitoring of behavior is an effective behavioral change technique (BCT) when combined with other techniques, such as shaping knowledge and social support [21,22]. Use of technology is a promising method for delivering these techniques [16]. The AHA recommends both 5 A’s counseling and technology-based interventions to improve cardiovascular health for individuals at moderate risk for disease [10].

PA interventions that utilize self-monitoring technologies have been shown to be efficacious [23-25]. Moreover, self-monitoring technologies are feasible to implement with 5 A’s counseling [23] and, thus, may help prevent the onset and progression/or progression of chronic diseases [26]. A self-monitoring technology commonly used is a pedometer [23,27-32]. Pedometers are cost-effective activity monitors that provide a simple method of promoting self-control via self-monitoring of steps [33]. Pedometer use is associated with improvements in PA, weight, and blood pressure [27-29]. These improvements may be sustained to prevent chronic disease risk factors (measured by the Framingham risk calculator) [31]. In a previous primary care intervention, individuals wearing a pedometer had significant increases in PA compared to usual care [34]. Ideally, technologies for preventing CVD should provide self-monitoring, education, personalized feedback, and should also be customizable [35]. Since standard pedometers cannot provide all of these features, they may not be optimal for CVD prevention.

More advanced pedometers, or electronic activity monitors (EAMs), are readily available on the market (estimated 3.3 million units sold in 2014) [36] and offer many features that standard pedometers do not. Like pedometers, EAMs count total steps, but they can also measure duration and intensity of PA. EAMs can sync wirelessly to an application (app) on a smart device (phone or tablet). The data it collects are displayed clearly and concisely through the app. EAMs are programmable in that the individual can set his or her personal activity goals [37]. Lyons et al [38] found that EAMs include numerous behavioral techniques commonly associated with PA change including: self-monitoring, feedback, goal-setting, planning, social support, social comparisons, commitment, instructions on how to perform a behavior, and information on consequences [39,40]. EAMs have the potential to change behavior alone, but they will likely be more successful if combined with structured engagement [41], such as a research intervention. Providing an EAM in addition to 5 A’s counseling shows promise in preventing CVD because: (1) an EAM can deliver counseling components that may not have been targeted by the physician [42]; (2) it provides adaptive PA goals based on progress, which is more effective than a static exercise prescription [43]; and (3) it can improve perceptions of relatedness by providing social support from other users.

### Specific Aims

Testing Activity Monitors’ Effect (TAME) on health (NCT02554435) will implement and evaluate a 12 week intervention that incorporates 5 A’s counseling and self-monitoring with an activity monitor among older primary care patients. Participants (n=40) will be randomized to receive 5 A’s counseling and an EAM system or 5 A’s counseling and a standard pedometer. Figure 1 shows the conceptual framework of TAME health (also outlined in Table 1). As a follow-up to the intervention, separate focus groups with research participants and primary care stakeholders will be conducted to further gauge the intervention’s feasibility and acceptability.

**Table 1 table1:** Conceptual constructs underpinning the research design.

Theoretical construct		BCT^a^	Intervention components		
			5 A’s counseling (both groups)	Pedometer	EAM
**Self-Determination Theory**					
	Autonomy	Goal-setting/intention formation	X		X
		Provide information on consequences of behavior in general	X		X
		Barrier identification/problem solving			X
		Action planning	X		X
	Competence	Provide feedback on performance	X	X	X
		Provide instruction	X		X
		Teach to use prompts/cues			X
		Self-control: Prompt self-monitoring of behavior		X	X
	Relatedness	Facilitate social comparison			X
		Social support	X		X

^a^ BCTs described are associated with Self-Determination Theory constructs based on previous research [22,44-46].

**Figure 1 figure1:**
[figure not shown]
Conceptual framework of the intervention.

## Methods

### Preliminary Studies

Several preliminary studies have shaped the proposed intervention. In a preexperimental pilot study, we recruited 10 sedentary older adults (55-79 years of age) into a six week intervention in which they received an EAM (UP by Jawbone), a mini tablet, and weekly counseling. Adding an EAM to the PA intervention was both feasible and acceptable within this older adult population that already used smart devices. There were nine out of the 10 participants that agreed or strongly agreed with the following statements: “I would continue to wear the monitor”; “I felt very confident using the tablet”; “The UP app encouraged me to view my steps”; and “It was convenient for me to use the UP app”. As a follow-up, we are completing a pilot intervention to determine changes in PA outcomes within this same population using an UP24 by Jawbone. We will compare PA outcomes between those who received the intervention to wait-list controls. Among the 38 participants to complete the intervention at this time, we found that nearly all used social support features of some kind. Several participants (8/38) even commented over 50 times across the 12 week period.

In addition to conducting PA interventions, we analyzed the content of EAMs. We evaluated 13 different EAMs and coded them for present BCTs [38] and validated their measurements of steps over the span of a week compared to research-grade activity monitors. We found that EAMs commonly incorporate important BCTs [38] and they reasonably estimate the number of steps per day.

The research team, led by [name], also conducted a systematic review of PA interventions that utilized EAMs [37]. This review evaluated different intervention methodologies and EAMs used by researchers. Findings suggested that EAM interventions produced equivocal results when compared to behavioral counseling alone. However, the devices investigated did not provide social support and used apps with fewer behavior change techniques than provided in Jawbone’s app. Compliance outcomes indicated that devices were regularly worn and utilized by participants [37]. Overall, our work to date suggests that EAMs are motivational devices that are acceptable for use by older adults and can change PA behavior in conjunction with behavioral counseling.

### Protocol

This protocol has been approved by the University of Texas Medical Branch (UTMB) Institutional Review Board (Protocol 15-0014, Version 5, 12/02/15) and is registered on a website (NCT02554435). This protocol also follows SPIRIT reporting guidelines (see Multimedia Appendix 1). The TAME health study design is displayed in Table 2.

We intend to recruit older primary care patients (n=40) to participate in the 12 week TAME health study. Primary eligibility criteria include: age (55-74 years), physically inactive (less than 60 min/week of PA), body mass index between 25-35, in good health as measured by the PA Readiness Questionnaire Plus (Par-Q+) [47], and access to a smart device. Eligibility criteria were determined based on our previous work using EAMs in this population. A smart device is operationally defined as a mobile phone or tablet using the iOS operating system or Android 4.3 or later. Reports suggest that 45% of adults over the age of 65 own a smart device [48]. Individuals will be excluded from the study if participation in PA is inadvisable by their doctor, they are involved in another PA intervention currently or within the past 6 months, utilized an EAM in the past 6 months, are unwilling to travel for scheduled visits, currently taking medications that affect body composition, a current smoker, report of alcohol or drug problem, institutionalizations for psychiatric illness within the last year, or do not consent. As advised in the Par-Q+ [47], prospective participants with comorbid conditions are eligible if they provide a letter from their physician stating that it is safe for them to participate in PA.

**Table 2 table2:** TAME health time frame.

		Study period				
		Enrollment	Allocation	Post allocation		Close-out
Study week		-12	0	1	12	12
**Enrollment**:						
	Eligibility screen	X	X			
	Informed consent	X				
	Allocation		X			
I**nterventions**:						
	5 A’s counseling		X	X		
	Pedometer			X	X	
	EAM			X	X	
**Assessments**:						
	Age (date of birth)	X	X			
	Gender	X	X			
	Education		X			X
	Cardiovascular risk		X			X
	PA	X	X	X		X
	Weight	X	X			X
	Body mass index	X	X			X
	Body composition		X			X
	Blood pressure		X			X
	Exercise motivation		X			X
	Health status and quality of life		X			X
	Physical function		X			X
	Psychological feelings		X			X
	Resting pulse		X			X

### Recruitment and Screening Procedures

Participants will be recruited from two clinics affiliated with a large university-based health care system. Recruitment started in October 2015 and will continue until all participants are enrolled. Prospective participants will be recruited from flier postings in waiting rooms and in patient rooms, direct solicitation from a recruitment table in the lobby, and through recruitment letters mailed to their home.

Patient eligibility will be determined by using a screening script. Screenings will be completed in person at the recruitment table or over the phone. Once patients are deemed eligible, the researchers will obtain informed consent. This will be done promptly after screening for eligibility at the recruitment table for patients screened in person. For patients screened over the phone, a researcher will arrange a meeting with the patient at their primary care clinic to obtain informed consent.

After obtaining informed consent, an assessment visit will be scheduled. Reminders about the orientation meeting will be sent via email monthly (for those recruited prior to the data collection start date of January 1, 2016) and one week prior to the scheduled meeting. In addition, participants will receive a phone call reminder the day before the meeting. Enrollment into the intervention is postponed until after January 1, 2016 to minimize seasonal variations in PA [49].

### Intervention Procedures

#### 5 A’s Counseling

All participants will receive brief PA counseling following the USPSTF 5 A’s model [17,18]. The counseling provided in this intervention is referred to the “5A-S model” for it emphasizes the importance of self-control. The counseling components included: assess, advise, agree, assist, arrange, and self-monitor. The brief PA counseling will occur during the private assessment visit at the participant’s primary care clinic, before randomization. An experienced PA counselor with a background in exercise physiology and training in motivational interviewing will conduct the counseling. To facilitate transition into clinical practice, participants will go through counseling at baseline and will be instructed to self-monitor with their assigned device for the subsequent 12 weeks. After counseling, the researcher will provide the participant with an exercise prescription to follow. A phone call will be arranged with the participant a week after the counseling to assess progress and resolve technical issues. Table 3 provides a description and an example of how each 5 A’s component will be operationalized in the current study.

**Table 3 table3:** Counseling components.

	Description^a^	Example
Assess	Ask about/assess behavioral risk	Review steps per day and minutes of PA per day from research-grade monitor
Advise	Advise participant to increase their PA to meet healthy levels	Compare current PA level to CDC guideline Define moderate and vigorous PA Suggest new PA goal
Agree	Reach agreement with the participant about appropriate weekly PA goal and a long term goal	Set weekly step goal Active planning of step goal Set long term PA goal
Assist	Teach behavioral change strategies	Identify social support Identify barriers Provide PA prescription
Arrange	Arrange a follow-up appointment to assess progress and any issues that arise	Schedule phone call in 1 week Review health changes Go through the “Agree” step on new weekly goal

^a^ The descriptions are modified from Whitlock et al [17].

#### Grouping the Participants

All participants will be given an activity monitor to encourage self-regulation of PA. After counseling, participants will be randomized to one of the two groups: pedometer or EAM group. A random number generator available on the Internet will be used to randomly allocate group assignment [50]. Assignment into the EAM group will be selected randomly by the generator using the following settings: 1 set, 5 unique numbers, numbers range from 1 to 10, and sorted lowest to highest. This process will be repeated for 3 more sets of numbers ranging from 11-20, 21-30, and 31-40. Each number represents a participant identification number selected to be in the EAM group. Group assignment will be written on a piece of paper wrapped in foil and carbon paper and concealed inside an envelope prior to group allocation. A blinded researcher will prepare all of the envelopes. After group allocation, participants will be given all intervention materials and detailed instructions on all intervention components. For participants in the EAM group, the researcher will also test the monitor and the participant’s smart device to ensure they are working properly. Due to the nature of the intervention, the participants and the accessor will not be blinded to group assignment after randomization.

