### Data Management

Participants will be thoroughly informed of study procedures and give informed consent prior to any data collection. All data and participant information will be kept in a locked file cabinet or stored as a deidentified file on a secured computer network. Data and participant information will be transported from the clinics to the office in a passcode protected folder or on an encrypted flash drive. Data will be linked with an identification number and will be stored separately from all personal information. Only authorized members of the research team will have access to data. Due to the small sample size, a data monitoring committee will not be utilized. Instead, the Principal Investigator will conduct data safety monitoring weekly.

Participants in the EAM group will be given deidentifiable accounts to be used by the UP app. The accounts will not provide names, images, or personal information of the participants. UP app accounts made by stakeholders, as part of their involvement in the focus groups, will not be deidentified and will include any personal information the individual discloses in the app (ie, name, images). Accounts will only be viewable by other study participants and the research team.

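### Allocation uses published fixed blocks of ten tied to participant IDs: up to about one allocation in six could be foreseen, and IDs lost before week 0 may use up slots

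*Protocol article*

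**What the plan says.** Grouping the Participants gives the rule in full. The generator settings are "1 set, 5 unique numbers, numbers range from 1 to 10, and sorted lowest to highest", and "This process will be repeated for 3 more sets of numbers ranging from 11-20, 21-30, and 31-40". The slot is the participant's ID: "Each number represents a participant identification number selected to be in the EAM group". Each assignment is wrapped in foil and carbon paper and "concealed inside an envelope prior to group allocation". Once an envelope is opened, "the participants and the accessor will not be blinded to group assignment after randomization".

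On timing, the section 5 A's Counseling places the counseling at the assessment visit in the "primary care clinic, before randomization". Table 2 puts enrollment at week -12 and allocation at week 0, with an eligibility screen at both. On IDs, Data Management says "Data will be linked with an identification number" but not when the number is issued. The planned size is 40: "Participants (n=40) will be randomized to receive evidence-based brief counseling plus either an EAM or a pedometer".

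**The concern.** Every block has the same known size and split. Foil and carbon paper hide what is in an envelope, but they cannot hide an assignment that follows from those already opened: once five of either arm have been used in a block, the rest of that block is determined.

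This matters because of what comes just before the envelope is opened. Table 3 has the weekly step goal, the long-term activity goal and the activity prescription set during counseling. Steps and activity minutes are primary variables in Table 4. A counselor who could foresee the arm might, without meaning to, set goals differently. The week-0 eligibility screen is a second route.

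Tying slots to participant IDs raises a separate issue. The list ends at ID 40. If the ID is given out at or soon after consent, anyone who drops out before week 0 takes a slot with them. The plan would then randomize fewer than 40, or need replacements for whom no assignment exists.

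**Working it through.** **Inputs.** From Grouping the Participants: 4 blocks, 10 IDs per block, 5 EAM per block. From Recruitment and Screening Procedures: two clinics, with no separate list per clinic described. The rate of ID loss before week 0 is not given; I assume 10% and show 5% to 20%.

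**The plan's own figure.** 4 × 10 = 40 slots, 4 × 5 = 20 EAM and 20 pedometer. This agrees with the planned 40.

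**Certain allocations, complete blocks, fully informed observer.** In a block of 2m with m per arm, the expected number of forced allocations is 2m/(m+1). For m = 5 this is 10/6 = 1.67 per block. Enumeration confirms it: of the C(10,5) = 252 possible orders, 140, 70, 30, 10 and 2 have 1, 2, 3, 4 and 5 forced allocations, so (140 + 140 + 90 + 40 + 10)/252 = 420/252 = 1.67. Over four blocks that is 6.67 of 40, or 16.7%.

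**Best-guess rate.** Always guessing the arm with more slots left is right in (5 + 2^10/(2 × 252) − 0.5)/10 = 65.3% of allocations.

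**What lowers the certain share.**
- Staff see only their own clinic's allocations (equal random split assumed): about 0.5%, by simulation.
- IDs are lost before week 0 and their envelopes stay sealed, so blocks stay incomplete (simulation): see the table.

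| Assumed loss | Mean randomized | Certain share | Chance of arm difference of 3 or more |
|---|---|---|---|
| 5% | 40 × 0.95 = 38 | 12.9% | 7% |
| 10% | 40 × 0.90 = 36 | 9.8% | 18% |
| 20% | 40 × 0.80 = 32 | 5.4% | 32% |

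The last column takes independent binomial losses from 20 EAM and 20 pedometer IDs.

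**Cost of the imbalance.** A 20:16 split keeps 4 × 20 × 16/36² = 1280/1296 = 98.8% of the efficiency of equal arms of the same total.

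**Is the ID issued before randomization?** Assessment Procedures has the armband and baseline questionnaire handed out about a week before the assessment visit. Physical Activity has the armband programmed from data taken at enrollment. Table 3 has armband results reviewed in counseling, before randomization. Data Management links data by ID. Together these imply an ID before allocation, but no sentence says so.

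**Alternatives** (simulation; the observer knows the possible sizes but not their order):

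| Scheme | Certain, of 40 | Best-guess rate |
|---|---|---|
| Fixed blocks of ten | 6.7 | 65.3% |
| 8, 10, 10, 12 in shuffled order | about 2.6 | about 65% |
| Sizes drawn freely from 8, 10, 12 | about 0.6 | about 64.5% |

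The freely drawn version need not end at 20:20; in about 36% of simulated lists the arms are unequal at 40. Smaller fixed blocks would be worse: 33.3% certain at size 4 and 25% at size 6.

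**The case against.** A reader might infer that staff will in fact know one allocation in six. The documents do not support that. It needs one person with the scheme and every earlier allocation in the block, at both clinics, and nothing says the counselor keeps or sees such a tally. The EAM section does create a research account to which every EAM participant is linked, so the information exists in one place, but who uses that account is not stated. One in six is therefore an upper bound.

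A reader might also add the two problems together. They partly offset each other: the more IDs are lost with envelopes sealed, the fewer allocations are forced.

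Nor do the documents establish that lost IDs use up slots. If the number from 1 to 40 is issued at randomization, none is lost. Conversely, if it is fixed at consent, the arm is already fixed to the person, and rescheduling a visit cannot move anyone to the other arm. What remains is influence on counseling and on the week-0 screen.

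Other safeguards are real. Envelopes are prepared by a separate researcher, counseling already precedes randomization, activity is measured by armband, and a blinded statistician analyses the primary outcome variables. Feasibility and acceptability are the main purpose, and Aim 2 declares the between-arm analyses exploratory. The remedy also leaves the best-guess rate near 65%.

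All of this limits the size of the problem. It does not justify keeping the fixed, published block, because mixed sizes around ten remove most of the certain allocations without making guessing easier.

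**Conclusion.** The point holds as a minor design weakness. With complete blocks and an observer who knows the scheme and all earlier allocations, 6.7 of 40 assignments (16.7%) are certain in advance. Under less complete knowledge the figure lies anywhere down to about 0.5%, and it is about 10% if 10% of IDs are lost with envelopes sealed. If IDs precede randomization, an assumed loss of 10% (5-20%) leaves about 36 (38-32) randomized; the arm imbalance itself costs little. Actual foreknowledge and actual loss of slots are possibilities that the plan leaves open, not facts that it states. It is still worth correcting, because Power Calculation intends the effect sizes from this pilot to inform larger trials, and any bias would carry over.

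**What to change.** - Have someone without participant contact draw the list, using mixed block sizes not disclosed to recruiting or counseling staff. Shuffling 8, 10, 10 and 12 totals exactly 40 and keeps 20:20. Drawing sizes freely from 8, 10 and 12 leaves fewer certain allocations but gives up the guaranteed 20:20.
- Number the envelopes 1-40 in order of allocation, separately from participant ID, so that someone lost before week 0 uses up no slot.
- Keep the existing order, with counseling completed before the envelope is opened.

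The cost is one paragraph in the protocol and a redrawn list. The article reports 8 participants enrolled by December 3, 2015 and an intervention start after January 1, 2016, so the change can be made before anyone is allocated. The statistical price is that the largest possible mid-block imbalance rises from 5 to 6.
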